### Harms and criteria for discontinuation or modification

2.5

Remimazolam and propofol are routinely used intravenous anesthetics for robotic laparoscopic surgery at our institution. Therefore, participation in our trial is not anticipated to introduce additional risk. However, hypotension and bradycardia may occur following administration of sedatives or opioids, and hypertension or tachycardia may arise in response to surgical stimuli. Hypotension (SBP <90 mmHg or MAP <65 mmHg) will be managed by reducing the remifentanil infusion rate. Severe hypotension (SBP <80 mmHg or MAP <60 mmHg) will be treated with intravenous ephedrine 5–10 mg or phenylephrine 30–100 μg. Hypertension (SBP >140 mmHg or MAP >100 mmHg) will be managed by increasing the remifentanil infusion rate, whereas severe hypertension (SBP >160 mmHg or MAP >105 mmHg) will be treated with intravenous nicardipine 300–500 μg or labetalol 5–10 mg. Bradycardia (HR < 45 beats/min) will be treated with intravenous glycopyrrolate 0.2 mg or atropine 0.25 mg, and tachycardia (HR > 100 beats/min) will be managed using intravenous esmolol 10–20 mg.

Study interventions may be modified or discontinued in cases of severe hypotension (SBP <80 mmHg or MAP <60 mmHg) unresponsive to protocol-directed vasopressor therapy, severe bradycardia (HR < 40 beats/min) unresponsive to atropine or glycopyrrolate, severe hypoxemia (SpO_2_ < 90% for more than 1 min), a severe allergic reaction to study medications, or if the attending anesthesiologist determines that continuation of the assigned intervention is unsafe. In such situations, anesthesia may be transitioned to an alternative regimen at the clinician’s discretion, and the event will be documented in the case report form (CRF).

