### Outcomes

2.6

The primary outcome of the study will be the time-weighted average (TWA)-MAP measured throughout anesthesia using an arterial line connected to a FloTrac™ sensor (Edwards Lifesciences, Irvine, CA, United States). For each participant, TWA-MAP will be calculated as the integral of MAP over elapsed time divided by the total observation duration, using the trapezoidal method. Data will be collected at approximately 1-min intervals when available, and measurements identified as technical artifacts (e.g., arterial line flushing, signal disconnection, damping artifacts, or recording errors) based on inspection of the arterial pressure waveform and corresponding clinical records will be excluded following data quality assessment. The primary analysis will compare TWA-MAP between the remimazolam and propofol groups to test the hypothesis that remimazolam-based TIVA will maintain a ≥20% higher intraoperative MAP than propofol-based TIVA.

Secondary outcomes will include the cumulative intraoperative burden of hypertension and hypotension. Hypertensive burden will be quantified as the area under the curve above the hypertension threshold (SBP ≥140 mmHg or MAP ≥100 mmHg), expressed in mmHg·min using the trapezoidal method. Hypotensive burden will be quantified as the area under the curve below the hypotension threshold (SBP <90 mmHg or MAP <65 mmHg), also expressed in mmHg·min. Group comparisons will assess whether remimazolam-based TIVA differs from propofol-based TIVA in hypertensive and hypotensive burdens. The time frame for secondary outcomes will extend from the start of induction to exit from the operating room.

In addition, intraoperative adverse hemodynamic events, including hypotension, hypertension, bradycardia, and tachycardia, will be recorded. Preoperative data will include patient characteristics, such as height, weight, age, diagnosis, scheduled surgical procedure, medical history, preoperative medication use, and baseline vital signs. Intraoperative data will include the surgical procedure performed, anesthesia duration, operative duration, degree of head-down tilt, vasopressin administration for bleeding control, estimated blood loss, fluid administration, and remifentanil dosage. Postoperative data will include post-anesthesia care unit (PACU) stay duration, PACU vital signs, and administration of additional medications, such as antiemetics and analgesics.

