### Statistical analysis

2.11

The primary outcome, TWA-MAP, will be analyzed using analysis of covariance, with group assignment as the fixed factor and baseline MAP, age, BMI, ASA-PS, and histories of hypertension and diabetes as covariates. Secondary outcomes, including hypertensive and hypotensive burden (area under the curve above or below predefined thresholds), will be compared between groups using Student’s t-test for normally distributed variables or the Mann–Whitney U test for non-normally distributed variables. Categorical outcomes, such as intraoperative hypotension, hypertension, bradycardia, tachycardia, PONV, and postoperative analgesic use, will be evaluated using the chi-square test or Fisher’s exact test, as appropriate.

Repeated-measures variables across prespecified time points (T0–T43), including HR, SBP, DBP, MAP, CO, CI, SVV, ETCO_2_, and arterial blood gas parameters, will be analyzed using generalized estimating equations (GEE) to assess group, time, and group-by-time interaction effects. An appropriate working correlation structure will be selected to account for within-subject correlations over time. As a sensitivity analysis, GEE analysis of serial blood pressure data will be performed to evaluate consistency with findings from the primary TWA-MAP analysis.

The primary efficacy analysis will follow the per-protocol (PP) principle, including all randomized participants who fully adhere to the study protocol. Participants with major protocol deviations, such as conversion to open surgery, administration of inhalational anesthetics, incomplete intraoperative hemodynamic monitoring, or early withdrawal, will be excluded from the PP analysis. Participants who discontinue the intervention due to serious adverse events will also be excluded. No intention-to-treat analysis is planned. The safety population will include all participants who receive at least one dose of the assigned anesthetic agent and will be analyzed according to the treatment actually administered.

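### Hypertensive and hypotensive burden are each one area tied to an SBP-or-MAP threshold, so these secondary outcomes have no unique value until one pressure curve is named

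*Protocol article*

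**What the plan says.** Section 2.6 (Outcomes) introduces the secondary outcomes thus: "Secondary outcomes will include the cumulative intraoperative burden of hypertension and hypotension". Hypertensive burden is the "area under the curve above the hypertension threshold (SBP ≥140 mmHg or MAP ≥100 mmHg), expressed in mmHg·min using the trapezoidal method". The low side reads: "Hypotensive burden will be quantified as the area under the curve below the hypotension threshold (SBP <90 mmHg or MAP <65 mmHg"), in the same unit. The window is also fixed: "The time frame for secondary outcomes will extend from the start of induction to exit from the operating room".

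The primary outcome in the same section, TWA-MAP, uses one signal (MAP) and divides its integral by the observation time.

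Section 2.11 (Statistical analysis) states that "hypertensive and hypotensive burden (area under the curve above or below predefined thresholds), will be compared between groups" by Student's t-test or the Mann–Whitney U test, depending on normality, with no covariates. Baseline MAP and five other covariates enter only the ANCOVA for the primary outcome.

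**The concern.** The article fixes the limits, unit, integration rule, window and test for each burden, but not the curve. SBP and MAP are different curves with different distances from their limits. An analyst could integrate SBP, integrate MAP, add the two areas or take the larger, and each choice is consistent with the text. The choice can move a patient between zero and non-zero burden and can change the order of patients, which is what a rank test uses.

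The burdens matter to the trial's message. The Discussion motivates the study by a retrospective report of more hypertension with remimazolam and more hypotension with propofol, and presents burden as part of the assessment of stability. The anesthesia providers are not blinded, so the curve should be settled on paper before the data are seen.

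A smaller point is that the comparison leaves out baseline MAP, although it is collected and already used for the primary outcome.

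**Working it through.** The article gives no numerical figure for the burden outcomes, so there is none to reproduce. The limits below come from Section 2.6; the pressure readings are illustrative.

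**1. The area depends on the curve.** For a signal X with limit c, the hypotensive area is the integral of max(c − X, 0) over time. The hypertensive area is the integral of max(X − c, 0). At constant pressure for T minutes each reduces to (distance beyond the limit) × T. With T = 10 min:

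| Episode (SBP/MAP) | SBP area | MAP area | Sum | Larger |
|---|---|---|---|---|
| Low, 85/62 | (90−85)×10 = 50 | (65−62)×10 = 30 | 80 | 50 |
| Low, 85/67 | 50 | 0 | 50 | 50 |
| Low, 95/60 | 0 | (65−60)×10 = 50 | 50 | 50 |
| Low, 88/55 | (90−88)×10 = 20 | (65−55)×10 = 100 | 120 | 100 |
| High, 150/95 | (150−140)×10 = 100 | 0 | 100 | 100 |
| High, 150/105 | 100 | (105−100)×10 = 50 | 150 | 100 |
| High, 138/104 | 0 | (104−100)×10 = 40 | 40 | 40 |

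All values are in mmHg·min. Two things follow. A record can be zero on one curve and positive on the other (85/67, 95/60, 150/95, 138/104). Order can also reverse: 85/62 is worse than 88/55 on SBP (50 against 20) and better on MAP (30 against 100).

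**2. Does any other section name the curve?** Section 2.9 lists MAP, and not SBP, among the continuous hemodynamic parameters. Section 2.10 lists MAP, and not SBP, among the values transcribed to the CRF. Section 2.9 also has vital signs recorded continuously, and Section 2.6 lists SBP among the recorded measurements. This leans towards MAP but does not settle it.

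**3. How much does case length matter?** A mean deficit of 0.2 mmHg over 120, 180 or 240 min gives 0.2 × 120 = 24, 0.2 × 180 = 36 or 0.2 × 240 = 48 mmHg·min. The total grows with time when per-minute exposure is constant. To see the effect on the comparison, burden was simulated as severity times duration. Both were log-normal, independent and with the same duration distribution in both arms; there were 26 patients per group, a Mann–Whitney test and a true shift of 0.75 log-scale SD in severity. The coefficients of variation (CVs) are assumptions, since the article gives none.

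| Severity CV | Duration CV | Type I error, cumulative | Power, cumulative | Power, time-averaged |
|---|---|---|---|---|
| 1.0 | 0.20 | 0.044 | 0.73 | 0.75 |
| 1.0 | 0.35 | 0.045 | 0.66 | 0.73 |
| 0.5 | 0.35 | 0.045 | 0.54 | 0.72 |

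When duration does not differ by arm, case length adds noise and does not inflate the error rate.

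**4. Division by duration is not neutral.** An area of 36 mmHg·min over 180 min averages 36/180 = 0.20 mmHg. Add 60 minutes within limits and the same episode averages 36/240 = 0.15 mmHg.

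**The case against.** A natural reading is that two areas are meant, each curve against its own limit. The article is also condensed, so a full protocol or analysis plan may hold the rule. The episodes above are invented, and nothing shows that the between-group conclusion would change. These points limit the weight of the finding but do not remove it. The article did not leave the definition to another document: it gave one with limits, unit, method and window, and that definition has more than one value.

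Three stronger readings are tempting, and the documents do not support them.

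- **A reader might infer that the undivided total is an error that biases the comparison.** Section 2.6 calls the burden cumulative on purpose, and total exposure is a legitimate quantity. Minutes within limits add nothing. Bias would need duration to differ by arm. Flumazenil is given in one arm only (Section 2.4), so the window may differ, but the article gives no durations by arm. Dividing by time changes the question and can dilute an episode.
- **A reader might infer that the unadjusted test is invalid.** It is valid under randomisation. Section 2.2 admits patients with SBP of 140–159 mmHg, above the hypertension limit, but this applies to both arms alike. Omitting baseline MAP costs precision only.
- **A reader might link the strict inequality in Section 2.5 ("Hypertension (SBP >140 mmHg or MAP >100 mmHg) will be managed by increasing the remifentanil infusion rate") with the ≥ in Section 2.6.** At exactly 140 or 100 mmHg the excess is zero, so no area changes. That difference is not part of this point.

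**Conclusion.** The point holds in limited form. As written, neither burden has a unique value, because one area is attached to two pressure signals and no section names the curve. Ten minutes of the same record can count as 30, 50 or 80 mmHg·min, or as 50 or 0. The effect on the between-group result cannot be sized from the article, which gives no expected burden and no joint SBP and MAP data. The primary outcome is not touched, and the article ranks these outcomes only as secondary.

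The absence of baseline MAP from the burden comparison is a missed gain in precision. Its size depends on how strongly baseline MAP predicts burden, which the article does not state. The dependence on case length justifies a supportive analysis, not a change of outcome; the power figures behind that rest on assumed CVs.

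**What to change.** - **Section 2.6:** define hypotensive and hypertensive burden on MAP alone, with the limits already stated there (<65 and ≥100 mmHg), matching the primary signal. Report the SBP areas (<90 and ≥140 mmHg) as separate, named variables.
- **Section 2.6:** keep cumulative mmHg·min as the stated outcome. Add burden divided by observation time (mmHg) as a supportive analysis only, because window length may differ between arms, and report window length by arm beside it.
- **Section 2.11:** replace the choice between t-test and Mann–Whitney with one named rank-based or ordinal regression model (for example proportional odds) containing group and baseline MAP.

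The cost is a change of wording. The recorded data and the sample size stay the same. The downside is that episodes low or high on SBP alone leave the main burden variable and appear only in the separate SBP variable.

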### Sample size

2.7

A previous study reported the median and interquartile range of intraoperative MAP during total intravenous anesthesia in patients receiving remimazolam or propofol (remimazolam: 81.3 [76.9–92.5] mmHg; propofol: 76.8 [67.8–82.5] mmHg) (Tsukimoto et al., 2024). Based on these findings, we will estimate the means and standard deviations using the method described by Wan et al. (2014). The required sample size was calculated using G*Power software (version 3.1; Heinrich Heine University, Düsseldorf, Germany). With 80% power and a two-sided significance level of 0.05, 26 participants per group are required (effect size = 0.7). To account for a 10% dropout rate, we will recruit a total of 58 patients.

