### Randomization, allocation concealment, and blinding

2.8

The random allocation sequence will be generated by an independent researcher who will not be involved in patient enrollment or perioperative management. A computer-generated randomization list will be created using an online tool (Research Randomizer; https://www.randomizer.org), assigning subjects identification numbers from 1 to 58 in a 1:1 ratio (remimazolam:propofol) without replacement. Simple randomization will be applied. No stratification or fixed block sizes will be used to minimize predictability and ensure equal allocation probability.

Allocation concealment will be ensured using sequentially numbered, opaque, sealed envelopes prepared in advance by the independent anesthesiologist responsible for randomization. The envelopes will be securely stored and opened only at the time of anesthesia induction. Investigators responsible for patient enrollment and anesthesia management will not have access to the randomization sequence beforehand.

After confirming eligibility and obtaining informed consent, the independent anesthesiologist will open the next envelope immediately before induction and disclose the allocation. An operating-room anesthesia nurse will prepare the study drug according to the assigned group.

The study will be conducted in a single-blind design. Participants and surgeons will be blinded to group assignment, whereas anesthesia providers and the operating-room anesthesia nurse will not be blinded due to the practical requirements of drug preparation and infusion management. To preserve blinding, syringes containing the study drugs will be placed in syringe pumps covered with opaque panels, preventing visualization of drug appearance or pump settings. Although remimazolam and propofol differ in appearance (colorless vs. milky white) and pump dose range (1–2 vs. 2.5–3.5, respectively), these characteristics will be concealed from participants and surgeons. Both groups will receive anesthesia guided to an identical depth target (PSI 25–50) using standardized anesthetic protocols to ensure comparability aside from drug assignment.

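### The stated 26 per group does not follow from two-sided 0.05, 80% power and d = 0.7: power is about 70% for the unadjusted comparison, and 26 matches a one-sided calculation

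*Protocol article*

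**What the plan says.** Section 2.7 of the protocol article takes intraoperative MAP from an earlier study ("remimazolam: 81.3 [76.9–92.5] mmHg; propofol: 76.8 [67.8–82.5] mmHg", median and interquartile range) and converts it to means and standard deviations by a published method. It names the tool: "The required sample size was calculated using G*Power software (version 3.1"). The result is "With 80% power and a two-sided significance level of 0.05, 26 participants per group are required (effect size = 0.7"). The total follows from that: "To account for a 10% dropout rate, we will recruit a total of 58 patients". Section 2.8 gives the allocation: "assigning subjects identification numbers from 1 to 58 in a 1:1 ratio (remimazolam:propofol) without replacement".

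Section 2.11 plans an ANCOVA of TWA-MAP with six covariates (baseline MAP, age, BMI, ASA-PS, hypertension, diabetes). Section 2.7 mentions no covariate correlation or variance reduction as an input. The limitations paragraph of the Discussion relies on the power calculation for the primary outcome and concedes limited power only for secondary and exploratory analyses.

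**The concern.** All the inputs of the calculation stand in one paragraph, so it can be checked directly. An effect size of 0.7 at two-sided 0.05 and 80% power usually needs a little over 30 per group, so 26 looks too small.

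This calculation is the only justification given for the size of the trial. If the claimed power is wrong, a null result on TWA-MAP would be read as coming from a trial with a 20% chance of missing the planned difference, when that chance is about 30%. The Discussion strengthens this reading by confining its caution about power to the secondary outcomes.

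**Working it through.** **Inputs (all from section 2.7, allocation from 2.8).** d = 0.7; alpha = 0.05 two-sided; power 80%; 1:1 allocation; dropout 10%.

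**Step 1: does the effect size reproduce?** The large-sample form of the conversion is mean = (Q1 + median + Q3)/3 and SD = IQR/1.35.

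- Remimazolam: mean (76.9 + 81.3 + 92.5)/3 = 83.57; SD (92.5 − 76.9)/1.35 = 11.56
- Propofol: mean (67.8 + 76.8 + 82.5)/3 = 75.70; SD (82.5 − 67.8)/1.35 = 10.89
- Pooled SD: √[(11.56² + 10.89²)/2] = 11.23
- d = (83.57 − 75.70)/11.23 = 7.87/11.23 = 0.70

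The effect size reproduces.

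**Step 2: does 26 per group reproduce?** G*Power uses the noncentral t distribution for a two-sample t-test. With n per group, df = 2n − 2 and noncentrality δ = d√(n/2). Two-sided power is P(|T| > t₀.₉₇₅); one-sided power is P(T > t₀.₉₅). At n = 26, df = 50, δ = 0.7 × √13 = 2.524, and the critical values are 2.009 (two-sided) and 1.676 (one-sided).

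| n per group | Two-sided power, d = 0.70 | One-sided power, d = 0.70 |
|---|---|---|
| 25 | 67.9% | 78.7% |
| 26 | 69.7% | 80.1% |
| 29 | 74.5% | 83.8% |
| 33 | 79.97% | 87.9% |
| 34 | 81.2% | 88.7% |

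The smallest n reaching 80% is 34 two-sided and 26 one-sided. The normal approximation gives 33 and 26. (With the unrounded d = 0.701, 33 per group just reaches 80% two-sided.) The stated 26 appears only in the one-sided column.

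**Step 3: could rounding of d explain it?** The largest value that rounds to 0.7, d = 0.749, gives 75.4% at 26 per group and needs 29. Reaching 80% two-sided takes d = 0.79 at 26 per group (0.79 × 11.23 ≈ 8.9 mmHg) or d = 0.75 at 29 per group (≈ 8.4 mmHg). The planned difference is 7.9 mmHg.

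**Step 4: could the conversion method explain it?** The finite-sample form of the conversion replaces 1.35 with a smaller constant, which raises the SDs and lowers d. The size of the source study is not in the article. Assuming 15 to 100 patients per arm, d is 0.63 to 0.69 and two-sided power at 26 per group is 61% to 68%. This moves further from 80%.

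**Step 5: could the planned ANCOVA explain it?** If the covariates explain a share R² of the outcome variance, the F test has noncentrality (d²n/2)/(1 − R²) with 2n − 8 denominator degrees of freedom for six covariates. Power of 80% two-sided requires R² = 0.224 at 26 per group and R² = 0.129 at 29 per group. If the covariates explained nothing, power at 26 per group would be 69.4%.

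**Step 6: dropout.** 52/0.9 = 57.8, so 58 is the correct inflation of 26 per group. This step carries the shortfall forward but adds no error of its own.

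**The case against.** Three points can be made in the plan's defence.

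First, the article does not say that a one-sided test was selected. That cause is inferred from an exact match. This stands, and the cause should be described as likely. The shortfall does not depend on it: whatever produced 26, two-sided 0.05, 80% and d = 0.7 do not.

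Second, the 70% figure describes an unadjusted t-test, whereas the primary analysis is an ANCOVA that includes baseline MAP. If the covariates explain some 22% of the variance with 26 per group, or 13% with 29, the trial does reach 80%. Such values are not implausible for blood pressure, and to that extent the actual power may exceed 70%. But the article gives no figure for the variance explained and does not use one in section 2.7, so the ANCOVA cannot support the number as printed.

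Third, 58 will be enrolled, so the power could be nearer 75% than 70%. That holds only if nobody is lost. The allowance from 26 to 29 is there to cover losses, and section 2.11 excludes major deviators, early withdrawals and participants with more than 5% missing values from the only efficacy analysis. The 29-per-group figure is therefore a best case, and it is still below 80%.

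**Conclusion.** The concern holds. The sample size in section 2.7 does not follow from its own inputs. For the unadjusted two-sided comparison at d = 0.70, power is 69.7% at the planned 26 evaluable per group and at most 74.5% if all 58 are analysed in equal groups, against the stated 80%. The type II error is about 30% instead of 20%, half as large again. Eight more evaluable participants per group (34 − 26) would be needed to meet the stated specification.

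These figures rest on the stated effect size and on equal groups. They do not credit any gain from covariate adjustment, because the article quantifies none. The lower range of 61% to 68% rests on an assumed size of the source study and is secondary. The paragraph is wrong as written and must be corrected, since it is the sole basis for the size of the trial.

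**What to change.** Correct section 2.7 in one of two ways, neither of which changes the number enrolled:

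- **Restate the power.** For example: *26 evaluable participants per group give 70% power (29 per group: 75%) to detect a standardised difference of 0.70 at two-sided alpha 0.05 with an unadjusted t-test.*
- **Base an 80% claim on the planned ANCOVA**, with its assumption stated and justified: the six covariates must explain at least about 22% of the variance in TWA-MAP with 26 per group, or about 13% with all 58 analysed.

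In either case the two-sided level should not stand beside a number that only a one-sided test gives. The limitations paragraph in the Discussion should then acknowledge the limited power for the primary outcome as well.

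The cost is the rewording of one paragraph and a sentence in the Discussion, and a less favourable power statement. If the sponsor wants 80% without relying on covariates, the size is 34 per group, or 68/0.9 = 75.6, so 76 in total with the same dropout allowance. That means 18 more patients and is not needed to make the text correct.
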